## Abstract

**Introduction:**

Membranous nephropathy is an autoimmune kidney disease and the most common cause of nephrotic syndrome in non-diabetic Caucasian adults. Rituximab is now recommended as first-line therapy for membranous nephropathy. However, Kidney Disease Improving Global Outcomes guidelines do not recommend any specific protocol. Rituximab bioavailability is reduced in patients with membranous nephropathy due to urinary drug loss. Underdosing of rituximab is associated with treatment failure. We have previously developed a machine learning algorithm to predict the risk of underdosing. We have retrospectively shown that patients with a high risk of underdosing required higher doses of rituximab to achieve remission. The aim of this prospective study is to evaluate the efficacy of algorithm-driven rituximab treatment in patients with membranous nephropathy compared to standard treatment.

**Methods:**

A multicentre, randomised, controlled, open-label, prospective superiority clinical trial will be conducted in 13 French hospitals. 130 consecutive patients with primary membranous nephropathy and active nephrotic syndrome will be randomised to either the standard protocol control group (two 1 g rituximab infusions on days 0 and 15) or the algorithm-driven rituximab treatment group. In the latter, the rituximab dose will depend on the algorithm-estimated risk of underdosing. Patients with an algorithm-estimated risk of underdosing ≤50% will receive 1 g of rituximab on days 0 and 15. Patients with an algorithm-estimated risk of underdosing between 51% and 75% will receive 1 g of rituximab on days 0, 15 and 30. Finally, patients with an estimated risk of underdosing >75% will receive 1 g of rituximab on days 0, 15, 30 and 45. The primary study outcome is the rate of clinical remission (complete or partial) at month 6 after treatment initiation. The secondary outcomes include clinical remission at month 12, immunological remission, proteinuria, albuminuria, serum creatinine, estimated glomerular filtration rate, phospholipase A2 receptor type 1 antibody titre, anti-rituximab antibody occurrence, lymphocyte count, serum rituximab level and related adverse events.

**Ethics and dissemination:**

The trial received ethics approval from the local ethics boards. The results of this study will confirm whether algorithm-driven rituximab treatment is more effective in inducing remission than the standard regimen and thus may contribute to improving management of patients with membranous nephropathy. The results of our study will be submitted to a peer-review journal.

**Trial registration number:**

NCT06341205 trial number. Registered on 2 April 2024.

Strengths and limitations of this studyThe artificial intelligence-based personalised rituximab treatment protocol in membranous nephropathy (iRITUX) trial is a multicentre randomised controlled trial conducted in 13 centres in France.The iRITUX trial is the first study to evaluate the value of artificial intelligence to guide treatment in membranous nephropathy.The iRITUX trial is not a double-blind trial due to the different treatment regimens, but the results will be analysed blinded to treatment allocation.

## Introduction

 Membranous nephropathy is an autoimmune kidney disease that represents the most common cause of nephrotic syndrome in non-diabetic Caucasian adults. The characterisation of membranous nephropathy as an autoantibody-driven disease and the identification of podocyte target antigens represent major advances in the diagnosis and follow-up of patients. Phospholipase A2 receptor type 1 (PLA2R1), the main target antigen, is involved in 70%–80% of cases of primary membranous nephropathy.^1^ Anti-PLA2R1 antibodies result in *in situ* deposits of immunoglobulins along the glomerular filtration barrier, which can be observed by immunofluorescence.^2 3^ These immune complexes lead to the activation of the complement system and induce the glomerular lesions responsible for nephrotic syndrome.^3^,^6^ These findings have rationalised the use of B cell-depleting drugs such as rituximab. Rituximab is a chimeric monoclonal antibody that targets the CD20 antigen on B cells. Over the last decade, rituximab has emerged as a first-line therapy for membranous nephropathy with proven safety and efficacy, and it is now listed in the 2021 Kidney Disease Improving Global Outcomes (KDIGO) guidelines.^7^ However, several factors may limit the efficacy of rituximab in the treatment of membranous nephropathy: (1) irreversible chronic glomerular damage; (2) the presence of antidrug antibodies and (3) reduced bioavailability.^8^,^13^ In fact, in autoimmune diseases other than membranous nephropathy, residual rituximab serum levels can be detected for 6–9 months after the first infusion. This is due to the recycling from endothelial cells via the neonatal fragment crystallisable receptor (FcRn).^14^ However, rituximab may be eliminated in the urine of nephrotic patients, as demonstrated in the comparison of two cohorts of nephrotic and myasthenic patients, paired by age, sex and weight, treated with the same rituximab regimen (1 g, 2-week interval). Residual rituximab level at month 3 was statistically lower in nephrotic patients compared with myasthenic patients.^11^ Rituximab was also detected in the urine of nephrotic patients from the 15th day after infusion.^11^ This urinary drug loss reduces rituximab exposure and may explain why the rituximab regimen of two 375 mg/m^2^ infusions did not demonstrate efficacy at month 6 compared with a non-immunosuppressive antiproteinuric regimen in the GEMRITUX study (NCT01508468).^15^ In contrast, a regimen of two 1 g infusions 2 weeks apart was associated with a significantly higher remission rate at month 6 than the GEMRITUX regimen.^16^ This high-dose regimen was associated with higher residual serum rituximab levels, more efficient B cell depletion and faster depletion of anti-PLA2R1 antibodies.^16^

Recently, we have shown that after two 1 g infusions of rituximab, patients with higher residual serum rituximab levels 3 months after rituximab infusion were more likely to achieve clinical remission at 6 and 12 months.^10^ Patients with a serum albumin level below 22.5 g/L at baseline had an 8.66-fold increased risk of having an undetectable rituximab level at month 3, demonstrating that the more severe the nephrotic syndrome, the more undertreated the patient will be. Therefore, it appears that optimisation of the rituximab regimen in membranous nephropathy should be considered. Early additional doses of rituximab may be beneficial in patients with a higher risk of rituximab underdosing to improve treatment bioavailability and increase the likelihood of remission. Evaluating the best dose schedule for rituximab in membranous nephropathy is one of the research recommendations of the 2021 KDIGO guidelines.^6^ In addition, the 2021 KDIGO guidelines do not specify which of the rituximab regimens is to be preferred.^6^ Tailoring the rituximab regimen to patient characteristics is an important issue.^17^,^22^ Repeated doses of rituximab, up to cumulative doses of 3000–6000 mg, according to autoantibody immunomonitoring, have been shown to be effective in inducing clinical remission while being safe.^17 23^ There is only one randomised controlled trial (NCT03804359) comparing personalised treatment with rituximab to the standard protocol.^22^ In this trial, treatment was personalised according to the PLA2R1 epitope spreading.

Nowadays, machine learning algorithms are increasingly used in medicine and especially in pharmacology to predict the exposure to a drug, the initiation dose or the interval between two infusions. We have developed a machine learning algorithm to predict the risk of rituximab underdosing.^24^ Based on age, sex, body surface area, anti-PLA2R1 antibody titre at day 0, serum albumin at day 0 and at day 15 and serum creatinine at day 0 and at day 15, this algorithm demonstrated its ability to predict rituximab underdosing at 3 months with an accuracy, sensitivity and specificity of, respectively, 79.4%, 78.7% and 81.0%. To validate the clinical relevance of our algorithm, we analysed the outcome of 45 patients with membranous nephropathy treated with rituximab. We retrospectively analysed the cumulative doses of rituximab received to achieve clinical remission and the time to achieve clinical remission according to the initial probability of rituximab underdosing proposed by our algorithm. Patients with a high initial probability of rituximab underdosing (>50%) had a longer time to remission (probability of rituximab underdosing ≤50%: 4.2±1.8 months vs 51%–75%: 8.4±4.6 months vs >75%: 10.7±5.9 months; p=0.002) and received higher cumulative doses of rituximab (probability of rituximab underdosing ≤50%: 2.0±0.0 g vs 51%–75%: 2.7±0.9 g vs >75%: 3.6±1.6 g; p=0.001).^24^

To prospectively evaluate our algorithm, we planned a multicentre, randomised study to evaluate the superiority and safety of an algorithm-guided rituximab regimen versus a standard regimen in patients with membranous nephropathy.

## Methods and design

### Design

This is a parallel, two-arm, randomised, open-label, multicentre (13 sites in France), prospective study comparing the superiority and safety of an algorithm-guided rituximab regimen with the standard regimen in adult patients with membranous nephropathy. The study will last 7 years, with a 6-year enrolment period and 1 year of follow-up. An overview of the study is shown in figure 1.

**Figure 1 F1:**
[figure not shown]
Detailed overview of the iRITUX study protocol. Created with Biorender.com. iRITUX, artificial intelligence-based personalised rituximab treatment protocol in membranous nephropathy; Mx, month-x; RTX, rituximab.

### Coordinating centre

The coordinating centre consists of:

A medical team (principal investigator (PI) and co-PI experts in membranous nephropathy) responsible for patient screening, recruitment and medical care. They are also responsible for validating the artificial intelligence-based personalised rituximab treatment protocol in membranous nephropathy (iRITUX) algorithm with a pharmacologist.A study coordinator is responsible for patient protocol visits, data entry and site coordination.A central laboratory team (one engineer and one technician) supervises sample collection and analysis for all sites.A sponsor team (project manager and research assistants) is responsible for all regulatory submissions, administrative coordination and monitoring.A central pharmacy specialising in clinical trials is responsible for shipping the investigational product to the sites.

### Inclusion criteria

Patients will be recruited if they fulfil the following criteria: age ≥18 years; membranous nephropathy diagnosed by either the presence of circulating anti-PLA2R1 or anti-thrombospondin type-1 domain-containing 7A (THSD7A) antibodies or kidney biopsy; active nephrotic syndrome defined by proteinuria >3.5 g/24 hours (or urine protein-creatinine ratio >3.5 g/g) and serum albumin <30 g/L at screening; estimated glomerular filtration rate (CKD-EPI formula) >30 mL/min/1.73 m^2^; indication for rituximab treatment according to the 2021 KDIGO and French guidelines; non-immunosuppressive antiproteinuric treatment at a stable dose for 2 weeks, including a renin-angiotensin-aldosterone system inhibitor, a diuretic and a low-salt diet at the maximum tolerated dose (ie, absence of orthostatic hypotension and no increase in serum creatinine >30%); social insurance; and signed informed consent (online supplemental file 1). Women of childbearing age must use an effective method of contraception up to 12 months after the last rituximab dose is received.

### Exclusion criteria

Patients with any of the following conditions will be excluded: secondary membranous nephropathy (related to cancer, infection, systemic lupus or drugs); pregnancy or breastfeeding; immunosuppressive treatment (including rituximab) in the 6 months prior to enrolment; the presence of anti-rituximab antibodies detected by the central laboratory; cancer under treatment; active serious infections; hypersensitivity to the active substance or excipients; severely immunocompromised patients who, in the opinion of the investigator, cannot receive more than two 1 g doses of rituximab; severe congestive heart failure or severe uncontrolled heart disease; persons deprived of liberty or incapacitated adults; patients who refuse to follow the algorithm recommendation approved by the referring nephrologist; and patients who, in the opinion of the investigator, cannot receive the dose regimen recommended by the algorithm (for tolerance or compliance reasons).

### Randomisation

After signing the informed consent and completing the screening visit to validate the inclusion criteria, participants will be randomised to one of the two treatment arms: (1) standard rituximab regimen and (2) algorithm-guided rituximab regimen. Centralised block randomisation will be balanced (1:1). Randomisation will be integrated into the electronic case report form (e-CRF) specifically designed for the study using the Research Electronic Data Capture (RedCap) software. Entering their personal access details to log in, the investigators will provide the necessary patient information (ie, the first letter of their first and last name and their month and year of birth) for random assignment to treatment using an online randomisation module (RedCap). The treatment group and inclusion number for the patient will be relayed to the investigator and the central laboratory team. The patient’s trial records will then be created automatically, allowing data to be entered.

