### Evaluation criteria

The primary endpoint is the clinical remission 6 months after the first rituximab infusion. Clinical remission is defined as a composite criterion, combining according to KDIGO guidelines: (1) complete clinical remission, defined as urinary protein/creatinine ratio (UPCR) <0.3 g/g in a morning spot urine sample and serum albumin >30 g/L and (2) partial clinical remission, defined as UPCR <3.5 g/g with a decrease >50% from baseline (ie, first rituximab infusion) and improvement or normalisation of serum albumin.

Secondary endpoints include complete clinical remission at month 12; partial clinical remission at month 12; immunological remission (ie, negative antibody titre by ELISA or negative indirect immunofluorescence) at month 3, month 6, month 9 and month 12; changes in proteinuria and albuminuria from baseline to month 3, month 6, month 9 and month 12; changes in serum creatinine and CKD-EPI estimated glomerular filtration rate from baseline to month 3, month 6, month 9 and month 12; changes in anti-PLA2R1 antibody ELISA titre from baseline to month 3, month 6, month 9 and month 12 (patients with PLA2R1-associated membranous nephropathy only); occurrence of anti-rituximab antibodies at month 3, month 6, month 9 and month 12; residual serum rituximab level at month 3 after the first rituximab infusion; recording adverse events related to treatment during study follow-up; changes in lymphocyte counts: B cells (CD19, transitional, mature and memory) and T cells (CD3, CD4, CD8 and T-Reg); changes in non-immunosuppressive antiproteinuric treatment during study follow-up; assessment of clinician satisfaction with the algorithm used to calculate the risk of rituximab underdosing (in the experimental group only); predictive rate (%) of the algorithm for rituximab underdosing in the control group; pharmacokinetics in all patients with serum creatinine and serum albumin levels, weight, anti-PLA2R1 and rituximab level at day 0, day 15, day 30, day 45, month 3 and month 6; and plasma cytokine levels after non-specific stimulation of innate and adaptive immunity cells in pg/mL (interferon (IFN)-γ, IFN-α, interleukin (IL)-12p70, IL-17A, IL-4, IL-5, IL-10, IL-1 and IL-6) at day 0 and month 6.

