### Follow-up

Study visits will be performed on day 15, day 30, day 45, month 3, month 6, month 9 and month 12 after the first dose (day 0) of rituximab for routine follow-up.

Clinical assessments (weight, blood pressure, heart rate, presence of oedema and change in concomitant medications) and biosamples will be collected at all follow-up visits, including a shipment to the central laboratory at each follow-up visit.

An individual participant may be discontinued from study intervention in the following

situations:

Participant decision. The participant is at any time free to discontinue treatment, without prejudice to further treatment.An adverse event that, in the opinion of the investigator, warrants discontinuation.

In the event of premature discontinuation of treatment, the patient should be encouraged to comply with protocol evaluations to allow intention-to-treat (ITT) analyses.

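### The central laboratory team that supervises sample analysis is told each patient's arm without a stated need, which leaves judgement-dependent secondary endpoints open to avoidable assessor bias

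*Protocol article*

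**What the plan says.** The trial is open-label because the arms can differ in the number of infusions. On allocation, the Randomisation section of the protocol article states: "The treatment group and inclusion number for the patient will be relayed to the investigator and the central laboratory team".

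The Coordinating centre section describes the recipient: "A central laboratory team (one engineer and one technician) supervises sample collection and analysis for all sites". The Follow-up section provides for samples at every visit, "including a shipment to the central laboratory at each follow-up visit".

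The only blinding statement is in the strengths and limitations box, which says that "the results will be analysed blinded to treatment allocation". It does not say who is blinded.

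Under Evaluation criteria, complete remission (one component of the primary endpoint) requires "urinary protein/creatinine ratio (UPCR) <0.3 g/g in a morning spot urine sample and serum albumin >30 g/L"; partial remission also uses the urine ratio and serum albumin. The secondary endpoints include immunological remission, defined by "negative antibody titre by ELISA or negative indirect immunofluorescence", anti-rituximab antibodies, the serum rituximab level, B- and T-cell subsets, and cytokines. One of these assays is expressly placed in the central laboratory: the Exclusion criteria refer to "the presence of anti-rituximab antibodies detected by the central laboratory".

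**The concern.** An open-label treatment does not require an open-label laboratory. When the people overseeing the assays know the arm, the decision to repeat a borderline result, the call on a weak immunofluorescence pattern, or the placing of a cytometry gate can differ between arms without anyone intending it. The group running the trial also developed the algorithm under test, so its staff know which result is hoped for.

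At stake is the credibility of the laboratory-read secondary endpoints. Immunological remission and anti-rituximab antibodies are each assessed at months 3, 6, 9 and 12. These endpoints would carry much of the mechanistic support for the algorithm, and a reader of the final report could not rule out that knowledge of the arm influenced them.

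**Working it through.** The article gives no figure for this point, so the check sets its sections side by side.

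**1. Does the laboratory learn the arm?** Yes. Randomisation sends it the treatment group as well as the inclusion number. This is a positive instruction, not a detail that the article leaves out.

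**2. Does the same team oversee the assays?** Yes, as far as the article goes. Coordinating centre describes two people who supervise sample analysis for all sites and gives no split into masked and unmasked staff. It does not say who performs each reading.

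**3. Does any stated laboratory task depend on the arm?** None was found.
- Follow-up lists the same visits for all patients: day 15, 30, 45 and months 3, 6, 9 and 12.
- Evaluation criteria takes pharmacokinetic samples from all patients at day 0, 15, 30, 45, month 3 and month 6.
- The algorithm uses day-0 and day-15 albumin and creatinine (Machine learning algorithm). Its prediction is also evaluated in the control group (Evaluation criteria), so these values are needed in both arms.
- The algorithm is run by the multidisciplinary staff (Experimental strategy), who are not described as the central laboratory.

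**4. Which endpoints are exposed?**

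| Endpoint | Read centrally? | Room for judgement |
|---|---|---|
| Anti-rituximab antibodies | Central at baseline; follow-up not stated but likely | Positive/negative call, repeat testing |
| Immunological remission | Not stated | Immunofluorescence reading; ELISA near the cut-off |
| Lymphocyte subsets | Not stated | Gating |
| Urine protein ratio and albumin (primary) | Not stated | Little; quantitative assays |

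**5. Scale, for illustration only.** With 1:1 allocation of 130 patients, each arm has 130 / 2 = 65.
- One sample called differently: 1 / 65 = 1.5 percentage points in that arm's rate.
- Three samples: 3 / 65 = 4.6 points.
- Five samples: 5 / 65 = 7.7 points.

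The counts of one, three and five are assumptions. The article gives neither the frequency of borderline samples nor a repeat-test rule. If fewer than 65 patients per arm are evaluable for an endpoint, each call weighs more.

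**The case against.** The strongest reply has five parts.

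- **A reader might infer that the blinding statement is contradicted.** The article does not support that. Saying that "the results will be analysed blinded to treatment allocation" most naturally refers to the statistical analysis, since Data collection has the frozen database passed to the statistician. An unblinded laboratory does not unblind a statistician. The statement is ambiguous, not contradicted.
- **A reader might also infer that the primary endpoint is compromised.** That does not follow either. It rests on quantitative assays that are not stated to be done centrally. The sample size and the interim stopping rule, which depend on it, are not called into question here.
- **Who reads the assays is not stated, and sample coding may be in a laboratory manual.** This is fair. It limits the exposure to anti-rituximab antibodies with reasonable confidence and to the other readings conditionally. It does not remove the explicit instruction to relay the arm.
- **The laboratory may have an unstated need.** In the experimental arm the day-15 values feed the algorithm before day 30, so urgent handling is conceivable. The control-arm prediction can be computed later, so it does not prove equal urgency. The article gives no such reason, however, and equal handling of all day-15 samples, or a request from the algorithm staff, would meet the need without disclosing the arm.
- **Masking would be incomplete.** Rituximab levels may hint at the arm, and they would do so in the patients given extra doses, who carry the treatment contrast. This stands as a limit of the fix. It does not justify telling the laboratory the arm of every patient.

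It is also true that no direction is stated for some endpoints, such as T-cell subsets, so bias need not always run the same way.

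**Conclusion.** The point holds as an avoidable weakness in design, confined to secondary endpoints. The article directs that the arm be given to the team supervising sample analysis and states no task that requires it. Anti-rituximab antibodies are the clearest exposure; immunological remission and lymphocyte subsets are exposed if they are read in the same laboratory. The primary endpoint is little affected.

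The size of any bias is unknown: the shift of about 1.5 points per differently called sample is arithmetic on 65 patients per arm, not evidence that such calls will occur. The conclusion assumes that no undisclosed coding scheme already hides the arm from assay readers, and that no unstated laboratory task needs it. It is a good-practice change worth making because it costs almost nothing, not a fault that threatens the trial's main result.

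**What to change.** - **Randomisation section:** send treatment group and inclusion number to the investigator and to the staff who run the algorithm. Send the central laboratory only the inclusion number and visit code.
- **Endpoint assays:** state that anyone reading immunofluorescence, ELISA, anti-rituximab antibodies or cytometry does not see the arm until database freeze.
- **Day-15 samples:** process and report them in the same way and on the same timetable in both arms, so that urgency does not reveal allocation.
- **Blinding statement in the strengths and limitations box:** name who is blinded (laboratory readers, statistician, or both).

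The cost is one change to the randomisation module's notification list and a few sentences of protocol text. Visits, samples, sample size, alpha, power and patient treatment are unchanged. There are two practical limits. Rituximab levels may still partly reveal the arm to whoever runs that assay. Any laboratory member who also belongs to the algorithm staff would have to be kept apart from assay reading, which may be awkward in a team of two.
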